**Methods:**

The study is a randomised controlled wait-list trial (RCT; *N* = 240). The intervention group will receive protocol-based MCT and work-focused interventions immediately after inclusion. The control condition is a wait-list control group. All patients will receive up to 12 weekly sessions. The study context is a Norwegian outpatient clinic part of a national programme aimed at reducing sick leave. The co-primary outcomes are change in RTW and symptoms of depression and anxiety at the end of treatment. In addition to self-report, sick leave will also be collected from national registries from 2 years prior to intervention to 4 years after intervention. Symptoms of depression and anxiety will be collected by self-report at pre- and post-treatment and at 6 and 12 months follow-up after treatment. A cost-effectiveness analysis will use total cost and quality-adjusted life-years as the secondary outcomes.

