### Secondary objectives

The secondary objective of the study is to determine whether the treatment is cost-effective compared to the wait-list condition and to examine other exploratory outcome measures. The questionnaires will be collected at screening, first treatment session and last treatment session. Follow-up questionnaires will be collected at 6 and 12 months post-treatment. The exception is change in diagnoses which will be evaluated by clinical interview at screening, before the first treatment session and after the last treatment session.

Measurements for the study’s secondary objective:
Changes in quality of life as measured by the EQ-5D-5L [37]Changes in metacognitions as measured by the Metacognitions Questionnaire 30 (MCQ-30) [38]Changes in bullying and victimisation as measured by the Negative Acts Questionnaire [39].Changes in work-related self-efficacy as measured by the Return to Work Self-Efficacy questionnaire (RTW-SE) [40].Changes in resilience as measured by The Resilience Scale for Adults (RSA) [41]Changes in subjective health complaints as measured by the Subjective Health Complaints questionnaire (SHC) [42].Change in diagnoses as measured by the Mini-International Neuropsychiatric Interview (M.I.N.I.) [43].

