### Study design

The study is an RCT comparing MCT and work-focused interventions given immediately after screening (< 1 week after assessment) with a wait-list condition. We chose a waitlist design as a “no treatment” control group is not feasible due to ethical reasons, and comparison with another active treatment was not feasible due to practical reasons. The intervention will be given as manualised treatment based on diagnostic-specific MCT as specified in the manual from 2009 by Wells [44]. Work-focused interventions will be based on the work module used in Lagerveld’s study but adjusted for a Norwegian context and MCT [18].

A summary flowchart of the procedure is found in Fig. 1. Treatment duration is up to weekly 12 sessions, but as the study takes place in a national health service outpatient clinic, the number of sessions may vary. The treatment primary outcome is measured at end of treatment or session 12 if treatment duration is longer, whichever comes first. In all, 240 patients who are on sick leave due to anxiety or depression at the time of enrolment will be recruited. The study uses a block randomisation with a stratification based on gender and degree of sick leave to ensure an equal balance of gender and sick leave across the conditions. Degree of sick leave indicates the percentage of ordinary working hours. Someone working half their normal number of hours would thus be on 50% sick leave. An equal number of patients are randomised to the treatment and wait-list condition. The waitlist condition group is subdivided into two equal groups that wait either 8 or 12 weeks before treatment, because in the sample there will be variation in the duration of the treatment intervention. The registry data will benchmark the current study against previous studies that have used CBT with regards to RTW. The maximum waiting time of 12 weeks is identical to the average waiting time at the clinic, to ensure that participation in the study does not delay treatment for patients. The reason for differentiating the waitlist condition is twofold. First, Norwegian law dictates that patients with moderate to severe depressive episodes should not wait longer than 8 weeks. Secondly, it is important to investigate if the duration of waiting in itself accounts for differences in change, e.g. whether shorter or longer waiting times improves outcomes.

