### Randomisation and blinding

After the initial screening session, eligible patients will be randomised using WebCRF, a web-based program provided by the Unit for Applied Clinical Research at the Norwegian University of Science and Technology (NTNU). The block randomisation is stratified on gender and degree of sick leave. The study will include 240 patients in all. Half of the patients will be allocated to the treatment condition (*n* = 120) and the other half to the wait-list conditions (*n* = 120). Half of the patients in the wait-list condition wait 8 weeks, the other half wait 12 weeks before commencing treatment. Because the treatment is offered in an ordinary outpatient clinic, the duration of the treatment will vary. To control for potential differences in treatment duration the wait-list condition also contained two different conditions.

Guidelines from the Norwegian Directorate for Health and Social Affairs state that patients who fulfil the criteria for a moderate depressive episode according to ICD-10 have the right to specialised health care within 8 weeks of referral [45, 46]. Thus, patients with this diagnosis will be allocated evenly between the treatment condition and the 8-week waiting condition. No patients with moderate depressive episode will be allocated to the 12-week waiting condition due to Norwegian law.

The randomisation procedure is performed by administrative personnel who otherwise are not involved in the patient’s treatment. Clinicians are not involved in the randomisation procedure. The initial assessment session is carried out by a different therapist than the one the patient sees for treatment. Blinding the treatment therapist to group allocation is not doable for logistical reasons (e.g. date of journal documents). Assessment of diagnosis at end of treatment using the Mini-International Diagnostic Interview is carried out by an independent clinician who has no prior contact with the patient.

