### Health economic analyses

The primary cost-effectiveness analysis will estimate total costs and QALYs for the 12-month follow-up period of the trial, using an intention-to-treat approach. Service use is not being collected in the trial and the cost-effective analysis will therefore be integrated within the trial and will include intervention costs alone. These will be estimated per patient and will include the cost of staff time, overhead costs and any other materials needed to deliver MCT. QALYs from baseline to follow-up will be estimated using the EQ-5D-5L. A Norwegian value set does not currently exist, and the English value set will be used [65]. EQ-5D-5L responses and index values will be reported and compared to the Norwegian general population norms [66].

Regression analysis will be used to estimate net costs and net QALYs and these estimates will be bootstrapped to generate 10,000 net pairs of costs and QALYs to inform the probability of cost-effectiveness. The incremental cost-effectiveness ratio (ICER), a joint measure of cost and health benefit, will be the key outcome, and a cost-effectiveness plane and cost-effectiveness acceptability curve will be plotted.

As the trial is not collecting service use to inform wider healthcare costs and the time horizon is limited, the economic evaluation will be furthered with the development of a decision analytic economic model which will synthesise trial data with the published literature. The model structure will be drafted considering the existing literature and the trial design, following which it will be reviewed and validated with clinicians. A literature review will be used to identify data not available within the trial (e.g. broader healthcare resource use and costs). As with the trial-based analysis, the key outcome will be the ICER (per QALY).

Guidance of the methods for economic models will be followed and the economic evaluation will adhere to reporting guidelines. Sensitivity analysis will explore uncertainty, in particular, the impact of using alternative measures of benefit, perspectives of cost and time horizons.

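### QALY baseline and horizon are not tied to randomisation, while the late EQ-5D-5L readings are dated from each patient's end of treatment, which falls 8 or 12 weeks later on the wait-list

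*Protocol article*

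**What the plan says.** All references are to the protocol article.

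- **Horizon.** Health economic analyses: "The primary cost-effectiveness analysis will estimate total costs and QALYs for the 12-month follow-up period of the trial". The same paragraph adds "QALYs from baseline to follow-up will be estimated using the EQ-5D-5L". Baseline is not defined there.
- **Reading times.** Secondary objectives, which covers the EQ-5D-5L: "The questionnaires will be collected at screening, first treatment session and last treatment session", and then "Follow-up questionnaires will be collected at 6 and 12 months post-treatment". The abstract and Retention and follow-up also date the 6- and 12-month points from treatment.
- **Start of treatment.** Study design has "MCT and work-focused interventions given immediately after screening", less than one week after assessment. For the control arm, Randomisation and blinding says "Half of the patients in the wait-list condition wait 8 weeks, the other half wait 12 weeks before commencing treatment".
- **Treatment received.** Abstract, Methods: "All patients will receive up to 12 weekly sessions". Wait-list patients are therefore treated too.
- **Estimation.** Health economic analyses: "Regression analysis will be used to estimate net costs and net QALYs", with bootstrapping of the cost and QALY pairs, by intention to treat. No adjustment for unequal observation time is mentioned. Sensitivity analyses are to vary the time horizon.

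**The concern.** A QALY is utility multiplied by time, so a between-arm difference is interpretable only if both arms are summed over the same span from the same origin. Here the last two readings are set on each patient's treatment clock, and the two arms' treatment clocks start 8 or 12 weeks apart. The text allows more than one choice of start and end. The readings that fit its own use of 12 months, as time after treatment, either give the arms unequal windows or leave out the period in which they differ by randomisation.

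Cost-effectiveness against the wait-list is the second of the trial's main hypotheses. Only intervention costs are counted and both arms receive the intervention, so the net cost may be small. The QALY difference would then largely decide the ICER, the cost-effectiveness plane and the acceptability curve.

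**Working it through.** The protocol article gives no utility, QALY or ICER figure, so there is nothing to reproduce. The check asks what each reading of the text would estimate.

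**Inputs from the document:** wait *w* = 8 or 12 weeks (half of the controls each, mean 10); a course of up to 12 weekly sessions, taken here as 12 weeks; last reading 52 weeks after treatment; intervention start taken as week 0 (stated as under one week).

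**Assumed, because the document does not give them:** utility before treatment *u0* = 0.4 to 0.7; gain with treatment *g* = 0.05 to 0.30; *u1* = *u0* + *g*. Utility rises linearly over the 12-week course and then holds. Controls stay at *u0* while waiting and then follow the same course (full catch-up). QALYs are areas under the curve, undiscounted.

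**Reading A: baseline is screening, end is the 12-month post-treatment reading.**
- Intervention: 12 + 52 = 64 weeks.
- Wait-list: 8 + 12 + 52 = 72 weeks, or 12 + 12 + 52 = 76 weeks.
- Credit for the extra weeks = mean utility × *w*/52. At utility 0.6 and 8 weeks: 0.6 × 8/52 = 0.09. At utility 0.8 and 12 weeks: 0.8 × 12/52 = 0.18.
- Under catch-up, the wait-list total is the intervention total plus *u0* × *w*/52. Net QALYs (intervention minus wait-list) are therefore −*u0* × *w*/52:
  - *w* = 8: −0.4 × 8/52 = −0.062 to −0.7 × 8/52 = −0.108.
  - *w* = 12: −0.4 × 12/52 = −0.092 to −0.7 × 12/52 = −0.162.

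**Reading B: baseline is the first treatment session.** The span is 12 + 52 = 64 weeks in both arms. Each arm is measured from the start of the same treatment, so under the assumptions above net QALYs are zero whatever the benefit of being treated earlier.

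**Reading C: one fixed period from randomisation, 52 or 64 weeks.** Net QALYs are +*g* × *w*/52:
- *w* = 8: 0.05 × 8/52 = +0.008 to 0.30 × 8/52 = +0.046.
- *w* = 12: 0.05 × 12/52 = +0.012 to 0.30 × 12/52 = +0.069.

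**One case across the readings** (*u0* = 0.6, *g* = 0.10, *w* = 10): A gives −0.6 × 10/52 = −0.115, B gives 0, and C gives +0.10 × 10/52 = +0.019.

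**If controls do not catch up.** Suppose they stay lower by *d* after treatment, the gap building over the 12-week course (equivalent to 6 full weeks) and lasting 52 weeks. Under Reading A the extra weeks are offset when *d* × 58/52 = *u0* × *w*/52, that is *d* = *u0* × *w*/58:
- *w* = 8: 0.4 × 8/58 = 0.055 to 0.7 × 8/58 = 0.097.
- *w* = 12: 0.4 × 12/58 = 0.083 to 0.7 × 12/58 = 0.145.

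A comparator that never improved would give a gain of *g* × 58/52 over 64 weeks: 0.112 for *g* = 0.1 and 0.223 for *g* = 0.2. The sign under Reading A therefore depends on catch-up.

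**The case against.** The strongest reply is that nowhere does the text say QALYs are summed over unequal spans. The paragraph opens with a single 12-month period for the trial, and the later phrase about baseline and follow-up can be read as governed by it. Baseline could be the first session, which gives equal windows, or the period could run from randomisation. Time origin, interpolation and truncation are also details that an article may leave to the analysis plan it mentions, and sensitivity analyses on the horizon are promised. Moreover, the readings are not all adrift from randomisation: the screening reading is taken just before it, and the wait-list first-session reading falls 8 or 12 weeks after it by design.

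Much of this stands. Unequal windows are one reading, not stated text. A reader might also infer that the extra weeks outweigh any plausible treatment gain and that the ICER would certainly carry the wrong sign. The documents do not support that: they give no utilities, and the inference needs a screening baseline, no time adjustment and full catch-up together.

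The reply does not remove the point. A first-session baseline equalises the windows only by discarding the waiting period. A period fixed from randomisation is sound, but the article does not state it and elsewhere uses 12 months for time after treatment. Varying the horizon in sensitivity analyses does not give the primary analysis a common origin. The article itself fixes both the horizon wording and the reading times, so the mismatch is more than an omitted detail.

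**Conclusion.** The point holds as a conditional one. The economic section leaves the origin and end of the QALY window unanchored to randomisation, in a design where treatment, and with it the last-session and follow-up readings, is staggered by arm.

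The 8- or 12-week difference in windows under a screening baseline follows from the document, given equal course lengths; the start within one week of assessment reduces it slightly. The size in QALYs rests on assumed utilities, and the reversal of sign on catch-up by the controls. Catch-up is plausible because controls receive the same treatment, but it is not established. The first-session alternative is no safer, because it estimates a contrast close to zero by construction. It remains open which of these the sponsor intends.

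**What to change.** State in the economic analysis plan:

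1. One window starting at randomisation, the same for costs and QALYs and for both arms, for example 52 weeks or 64 weeks.
2. QALYs as the area under the EQ-5D-5L curve, interpolated between the existing readings (screening, first session, last session, 6 and 12 months after treatment) by their actual dates, and truncated at the same week in both arms.
3. Adjustment of net QALYs for the screening EQ-5D-5L value, named as the baseline.

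This changes wording only and needs no new data. With 52 weeks, the window ends no later than the 12-month post-treatment reading for every patient who provides one. With 64 weeks, intervention patients who finish before week 12 would have their last reading before the window closes.

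The cost is follow-up left out of the primary economic analysis. At 52 weeks this is about 64 − 52 = 12 weeks in the intervention arm and 72 − 52 = 20 or 76 − 52 = 24 weeks on the wait-list. At 64 weeks it is none in the intervention arm and 8 or 12 weeks on the wait-list. The later data can go into the time-horizon sensitivity analysis already planned.

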### Dissemination

A trial publication board will meet regularly, and the board sets the publication policy for the trial. Currently, three Ph.D. candidates are expected to utilise data from the study and publish articles in peer-reviewed journals.

## Discussion

The aim of this trial is to investigate the impact of MCT and focused interventions on sick leave and symptoms of depression and anxiety, and whether this treatment is cost-effective. This is the first RCT to examine the effect of MCT and adapted work-focused intervention, contributing high-quality evidence on a novel approach aimed at a significant public health issue. As the study will include 240 patients, this is a fairly large clinical trial, and the long follow-up period will yield a considerable amount of outcome data.

A recurrent issue in the literature is that therapy and work interventions vary greatly between studies and that the therapy and the interventions are not adequately described, making comparison and replication difficult. The present protocol attempts to address this issue by describing the content and structure of a well-defined therapy and work intervention in detail.

There are many factors contributing to sick leave, and any given treatment is unlikely to address all issues for all patients. The large amount of outcome data in the present study can help to describe some associations between contributing factors, and thus inform future research questions. Similarly, registry data collected up to 4 years after completion of the trial will give reliable data on this patient group beyond the immediate end of treatment.

The relatively short wait-list period in the trial design may pose a challenge to detecting differences in outcomes. The Norwegian regulation regarding moderate depression stipulates that 8 weeks is the maximum delay before treatment onset after diagnostic evaluations. The intention in the regulation is to assure that patients with moderate depression experience as little delay in the onset of treatment as possible. This regulation may be specific to Norway and may complicate comparisons with results from similar studies from other countries. It is a limitation with the study, however, the setting of research project is a regular outpatient clinic, and regulations of clinical activity also has implication for research. A potential strength of the project precisely related to the setting is the relatively high ecological validity. On this note, it is worth mentioning that our previous observational study had a similar time-frame and showed good results for sick leave and symptom reduction in the intervention versus wait-list condition [34]. It is also the case that the current trial is monocentric. For the future, it would be of interest to replicate the study in a multicentre trial. Lastly, the economic impact of mental health problems and reduced employment is a significant societal expense. The result of the trial’s economic analyses can help inform policy decisions and clinical practice. As the ability to work is an important determinant of health and well-being, we believe patients suffering from depression and anxiety will benefit from expanding the evidence base on specialised care that includes interventions aimed at work-functioning.

## Trial status

The trial is carried out by Diakonhjemmet Hospital in cooperation with the Norwegian University of Science and Technology with additional funding from Sitftelsen Dam and the Norwegian Southern and Eastern Regional Health Authority. Recruitment began 1 January 2018 and was completed in May 2021. This protocol has been written to comply with the Standard Protocol Items: Recommendations for Interventional Trials (SPIRIT) statement (see Additional file 1 “SPIRIT checklist”). The final report will follow the Consolidated Standards for Reporting Trials (CONSORT) statement. Protocol version: Original, issued 25 August 2020.

## Data Availability

Data management including access is handled by Diakonhjemmet Hospital.

## Abbreviations

AUDIT: Alcohol Use Disorders Identification Test
BAI: Beck’s Anxiety Inventory
BDI-II: Beck’s Depression Inventory-II
CAS: Cognitive attentional syndrome
CBT: Cognitive behavioural therapy
EQ-5D: Euro-Qol 5D
ICER: Incremental cost-effectiveness ratio
M.I.N.I: Mini-International Neuropsychiatric Interview
MCQ-30: Metacognitive Questionnaire 30
MCT: Metacognitive therapy
NAQ-R: Negative Acts Questionnaire Revised
NTNU: Norwegian University of Science and Technology
QALY: Quality-adjusted life year
RCT: Randomised controlled trial
RSA: Resilience Scale for Adults
RTW: Return to work
RTW-E: Return to Work Expectation
RTW-SE: Return to Work Self-efficacy
SAPAS-SR: Standardised Assessment of Personality Self-report
SHC: Subjective Health Complaints
SNAQ: Short Negative Acts Questionnaire
W-CBT: Work-focused cognitive behavioural therapy
MCT: Metacognitive therapy
